# The ReThink study: a 3-arm parallel randomized trial of cognitive bias modification, with and without adherence promotion, for adolescent anxiety disorder: trial design and protocol

**DOI:** 10.1186/s12888-019-2296-z

**Published:** 2019-10-22

**Keywords:** Anxiety disorder, Adolescent, Cognitive bias modification, Randomized controlled trial

## Abstract

**Background:**

Anxiety disorders are the most common mental health problem among youth, contribute to reduced quality of daily life, and are associated with high rates of comorbidity. However, treatment rates for anxiety are very low, causing a sizeable treatment gap. There is an immediate need to identify treatment interventions that are effective, affordable, and can be delivered easily to the youth population. Cognitive Bias Modification (CBM) is one potentially effective intervention that could reach youth on a large scale, especially when self-administered at home. Thus, we aim to assess the benefit of CBM to treat youth anxiety. Further, we aim to test whether adding an adherence promotion (AP) component to the CBM intervention can improve outcomes, and whether CBM delivered both with and without the AP component is cost effective.

**Methods:**

This is a 12-month randomized controlled trial (RCT) conducted within an existing healthcare system. Potentially eligible youth (ages 12 to 17) will be identified by reviewing the electronic health record (EHR) for clinical anxiety diagnoses, which are then confirmed via research interview. We aim to enroll 498 participants and randomize them 1:1:1 to one of three arms: Arm 1 is a Low-Ratio version of the CBM program (nearly identical to the other CBM versions, but minimally effective); Arm 2 is a High-Ratio “active” CBM program; and Arm 3 is the High-Ratio CBM program with an added AP component. Participants will complete assessments at baseline, 1-, 3-, 6- and 12-months post-baseline. Youth in all three arms will self-administer the CBM program at home and will be asked to complete twelve intervention sessions over a four-week period. Arm 3 participants (High-Ratio CBM + AP) will also receive up to four telephone calls from phone coaches during the intervention period to provide technical assistance, encouragement, and motivational enhancement to increase adherence. The primary clinical outcome will be anxiety remission at 6-month follow-up.

**Discussion:**

This study protocol describes the method and design for an RCT to test whether self-administered CBM both with and without adherence promotion can be an effective at-home treatment for anxious youth.

**Trial registration:**

ClinicalTrials.gov: NCT02156531, First Posted June 5, 2014.

## Background

Approximately 1 in 3 adolescents meet criteria for an anxiety disorder by age 18, making anxiety disorders the most common mental health problem among youth [1]. These disorders interfere with daily life, have high rates of medical and psychiatric comorbidity [1, 2], are associated with high health care costs [3, 4], and are comorbid with substance abuse, depression and functional impairment in adulthood [5]. Additionally, anxiety has the lowest treatment rate of any mental disorder in childhood and adolescence [6, 7]; less than one-third of youth identified with anxiety received any intervention [8]. This disparity between high prevalence and low treatment makes addressing this “care gap” a significant public health priority.

What treatments are known to be effective for youth anxiety disorder? While there is a large body of evidence supporting the efficacy of both cognitive behavioral therapy (CBT) and medications such as selective serotonin reuptake inhibitors (SSRIs) for anxiety disorders, there are significant patient, intervention, and organizational barriers to youth receiving these evidence-based treatments (EBTs). Youth experiencing anxiety disorders typically have multiple psychosocial stressors and comorbidities [9] that inhibit active engagement in CBT. CBT demands a substantial time commitment on the part of both patient and therapist, is expensive to deliver, and is not a widely available treatment option due to the lack of qualified therapists available (particularly in rural areas). Although antidepressant (AD) medications are accessible and easier to administer, significant barriers leading to treatment nonadherence have been well documented, such as concerns about adverse effects, fears of dependence, and the often weeks- or months-long delay before therapeutic response [10]. As a result, there is an immediate, unmet need to identify and disseminate effective treatment interventions that are accessible, affordable, have few or no negative side effects, and can be delivered easily to the youth population.

One potentially effective anxiety intervention that could reach affected youth on a large scale is computerized Cognitive Bias Modification (CBM). The role of cognitive bias in the development and maintenance of anxiety has been well established from basic cognitive research [11, 12]. Biased attention towards real or perceived threat is associated with anxiety due to hypervigilance, rumination, and inaccurate appraisal of risks. Past research has shown that this biased attention towards negative rather than positive or neutral stimuli increases anxiety, and is related to generalized anxiety, social phobia, and trait and state anxiety [13, 14]. CBM is one of several related treatments that aim to retrain individuals to focus attention on positive or neutral stimuli, rather than negative or threatening stimuli. CBM is designed to adjust attentional bias at this early stage of processing, when patients are engaged in hypervigilance and over-attention to threatening cues. At this early information processing stage, training to focus attention away from threat has been shown in early studies to reduce anxiety symptoms [15–18]. The effects of CBM delivered under optimal conditions have been shown to be similar in magnitude to CBT and SSRI treatment for anxiety [15], and shows promising results in reducing anxiety in adult populations [18–22].

In youth populations, prior studies of CBM have shown significant symptom improvement in both anxiety and depression when delivered in a lab-based or residential treatment facility setting [15, 23–25]. However, because CBM is a self-administered computerized program, one advantage is the ability to disseminate it to patients at home, as it has a lower cost and time burden to implement than in-person administration. However, few studies have examined the effect of CBM in a real-world setting. Therefore, it is critical to test this promising treatment in conditions similar to those in which it could be eventually disseminated, as it is sometime the case that intervention effects observed in highly controlled trials diminish when evaluated in real world circumstances [26].

At least one study examined the efficacy of CBM delivered at home [22]. In that study, Carlbring and colleagues examined self-administered internet-based CBM in a home setting in 79 adults with social anxiety. These researchers did not find a significant difference between groups at post-treatment and 4-month follow-up. Neubauer and colleagues [27] also failed to find a benefit of Internet, home-delivered CBM versus the control condition at 4-month follow-up among their study of individuals with social phobia (*n* = 56).

One explanation for the weaker effects in self-administered CBM may be poor patient adherence when the intervention is delivered at home when compared to staff-facilitated lab settings. As a higher number of completed training sessions is associated with larger effect sizes [28], and in some studies, explicit staff-administered instructions for completing the CBM sessions may improve efficacy [29], another possible explanation for the lower efficacy of self-administered CBM may be reduced dose.

While most previous research of self-administered CBM has been conducted with adults, a number of studies have examined self-administered CBM among anxious youth [23, 24]. However, the effectiveness of self-administered CBM among youth remains to be tested on a large-scale basis. Therefore, to address these gaps in the literature, we aim to conduct a large efficacy-effectiveness trial within an existing health-care system to assess the benefit of computerized CBM to treat youth (ages 12–17) with one or more clinical and research-confirmed anxiety diagnosis. We identify this trial as having an efficacy-effectiveness design because we implement rigorous research inclusion criteria and outcome assessment, and will examine CBM mediational mechanisms (efficacy features), but at the same time we enroll participants who are seeking routine clinical care for anxiety in a large active healthcare system, have clinical anxiety diagnoses, and the intervention is self-administered (effectiveness features). We aim to test whether a telephone-based adherence promotion (AP) program can improve adherence and CBM dose to the levels obtained when CBM is delivered in laboratories. To our knowledge, this study will be the first to test this added component. The AP protocol consists of 1 to 4 brief telephone calls to provide explicit instructions to complete the sessions, offering additional support and motivational enhancement techniques [30–32] when warranted, and problem-solving barriers to completing the sessions.

We will conduct a randomized controlled trial of three arms, each corresponding to different versions of the CBM program: Low-Ratio CBM (Arm 1; a control/low dose version of CBM), High-Ratio “conventional” CBM (Arm 2), and High-Ratio CBM with AP (Arm 3). Ratio refers to the proportion of CBM trials in each session that are intended to retrain negative bias (details below). All versions of the intervention will be self-administered on participants’ home computers, as this would be the setting of eventual dissemination of this intervention. We hypothesize that the two High-Ratio CBM arms (Arms 2 and 3) will lead to greater rates of remission for anxiety diagnoses and greater improvement of symptoms and functioning, compared to the Low-Ratio CBM condition (Arm 1). Additionally, we hypothesize that the High-Ratio CBM with AP arm (Arm 3) will result in greater rates of anxiety remission and symptom improvement, compared to the High-Ratio CBM-only arm (Arm 2).

If we find that self-administered computerized CBM is an effective treatment option in real world settings, it will be important to consider whether broad dissemination and implementation is feasible. To evaluate this, we will compare the costs and outcomes of delivering High-Ratio CBM both with and without the adherence promotion component in an incremental cost effectiveness analysis. Specifically, we will examine whether High-Ratio CBM with AP will have benefits that warrant the additional cost of implementation (i.e., the additional labor costs associated with the AP portion of the intervention).

## Methods

### Design

This study is approved by the Kaiser Permanente Northwest (KPNW) Internal Review Board (IRB) in Portland, Oregon. This study is a randomized controlled trial (RCT), with participants blinded to the type of CBM they receive (low vs. high ratio) but not blinded regarding receipt of AP contacts. All evaluators are blinded to participant study condition.

Participants will be randomized via computer-programming to one of three arms in a 1:1:1 ratio, stratified by age at recruitment (< age 15 vs. > = age 15) and minority status (white non-Hispanic vs. all others). Assignment will be conducted with computer-generated random block sizes of 6 or 9, masked from study staff.

Arm 1 is a Low-Ratio version of the CBM intervention, nearly indistinguishable from the other CBM version but with a lower proportion of trials that shift attention to the neutral stimuli (details below). Arm 2 is a High-Ratio CBM program, with a higher proportion of trials shifting attention to the neutral stimuli. Arm 3 is the same High-Ratio CBM program but with a component consisting of adherence promoting (AP) telephone calls from a study phone coach, from 1 to 4 total as needed. All CBM programs are self-administered on participants’ home computers.

The primary clinical outcome will be diagnostic remission at 6-month follow-up from all anxiety diagnoses present at baseline, as confirmed by the Anxiety Disorders Interview Schedule (ADIS) (see below). The secondary clinical outcomes will be the PARS, SCARED, attention bias, depression (PHQ-9), psychopathology severity (CGI-S), and psychosocial functioning (CGAS). We will also determine whether there are differences in treatment acceptability (PAQ) and satisfaction (CSQ-8). Another secondary outcome will be cost-effectiveness of the CBM intervention, as measured in incremental cost per anxiety-free-day (AFD) and cost per quality adjusted life year (QALY). Additional analyses will test whether baseline CGI-S, PHQ-9 (depression), severity of cognitive bias (ADP), gender, socio-economic status, and race/ethnicity moderate the effect of the intervention on the primary outcome. Additionally, we will test whether attention bias mediates the effect of the intervention on the 6-month remission rate and anxiety outcomes (PARS and SCARED). Lastly, we will examine whether CBM process variables (i.e., number of trials [dose], acceptable error rates, reaction time) is associated with CBM outcomes.

### Population and recruitment

Youth between the ages 12 to 17 years old will be enrolled from the KPNW healthcare organization, a large, non-profit health maintenance organization in the Pacific Northwest region of the USA. We aim to enroll a total of 498 participants in the study.

Potentially eligible youth will be identified by reviewing the healthcare organization electronic health record (EHR) for anxiety diagnoses (general anxiety disorder [GAD], anxiety disorder unspecified, or social phobia [SP], and/or separation anxiety). These are not qualifying criteria themselves, but a preliminary case-finding stage that identifies youth who are likely study eligible whom we will approach for recruitment. This initial EHR stage is meant to improve case-finding efficiency. Teen and parent participants will be recruited by mail, with a follow-up telephone call. Interested families will complete a brief, initial phone screening interview to determine if they meet preliminary inclusion and exclusion criteria. If preliminary eligibility criteria are met, parents and youth will give consent to participate in the full baseline assessment.

Inclusion criteria for this study include: age between 12 and 17 years old at enrollment; a research anxiety diagnosis confirmed by the ADIS at the baseline interview (see below); youth and parent able to complete assessments in English; youth access to a Windows home computer with Internet access. Exclusion criteria include: youth diagnosis of psychotic disorder; significantly impairing learning disorder or processing problem, such that completion of study procedures would be difficult; ADHD (except if symptoms are stable and controlled by medication for at least one month prior to enrollment); or youth primary complaint of condition other than anxiety. Comorbid diagnoses leading to study exclusion will be confirmed by reviewing the EHR.

We considered whether to require a minimum level of cognitive bias at baseline as an inclusion criterion. Based on the literature at the time of our proposal, higher pre-treatment levels of negative bias were associated with improved outcomes [33], although this question has been little tested in anxious youth. Ultimately, we elected to not require a minimum bias level, for several reasons. First, the literature on this issue is suggestive but not definitive, especially for youth. Second, the effectiveness nature of this trial argues for the broadest inclusion possible with the most representative sample. Third, including all youth regardless of baseline bias provided an opportunity to test this relationship in a very large sample.

### Assessments

After the preliminary screening call, interested and potentially eligible participants will complete a baseline interview where final eligibility is determined. All measures at baseline will be administered to parent and youth participants over the phone, prior to randomization. See Table 1 for the assessment schedule.

**Table 1 Tab1:** Assessment Schedule

Measures	Administration time (mins)	Respondent	Youth or Parent Sx	Timepoints*					
				S	T0	T1	T2	T3	T4
Phone eligibility screen	15	Y P	Y	x					
Youth Anxiety measures									
Anxiety Dx Interview Schedule-Child (ADIS-C)**	50	Y P	Y		x			x	x
Pediatric Anxiety Rating Scale (PARS)	15	Y P	Y		x	x	x	x	x
Screen Child Anxiety Relate Emotional Dx (SCARED)	10	Y P	Y		x	x	x	x	x
Child Avoidance Measure–Self Report (CAMS)	5	Y	Y		x	x	x	x	x
Child Avoidance Measure–Parent Report (CAMP)	5	P	P		x	x	x	x	x
Depression measures									
Patient Health Questionnaire (PHQ-9)	10	P	Y		x	x	x	x	x
Patient Health Questionnaire (PHQ-9) (Parent self-report)	5	P	P		x	x	x	x	x
Other psychopathology, improvement measures									
Clinical Global Improvement –Severity (CGI-S)	5	Y	Y		x				
Clinical Global Improvement –Improvement (CGI-I)	–	Y	Y			x	x	x	x
Psychosocial functioning, quality of life measures									
Children’s Global Adjustment Scale (CGAS)	–	Y	Y		x	x	x	x	x
Healthcare services, economic measures									
Child & Adolescent Services Assessment (CASA)	5–10	Y P	Y			x	x	x	x
EQ5D	5	Y P	Y		x	x	x	x	x
Other measures									
Demographics	5	P	–		x				
State Trait Anxiety Inventory (STAI) – State	5	P	P		x	x	x	x	x
Peterson Pubertal Development Scale (PDS)	5	Y	Y		x				
Insomnia Severity Index (ISI)	5	Y	Y		x	x	x	x	x
Participant Acceptability Questionnaire (PAQ)	5	Y P	–			x			
Client Satisfaction Questionnaire (CSQ-8)	5	Y P	Y			x			
U Rhode Island Change Assessment (URICA-S)	5	Y	Y		x	x			
Instrumental Variables (IV)	5	Y	Y		x				
CBM session review	5	Y	Y			x			
Treatment adherence and process data	–	–			x	x	x	x	x

*Timepoints: S = Screening; T0 = Baseline; T1 = 1-month follow-up; T2 = 3-month follow-up; T3 = 6-month follow-up; T4 = 12-month follow-up

** Primary outcome, ADIS anxiety and depression modules only

**health care utilization data obtained from the HMO administrative data system

Dx = diagnoses/disorders, Sx = symptoms, Y=Youth, P=Parent, I=Interviewer

Each assessment wave will take between 1 and 2 h each for youth and parents to complete. Youth and parent participants will complete four follow-up assessments: “post-treatment” at the end of the active intervention period one month after enrollment; and 3-month follow-up, 6-month follow-up, and 12-month follow-up. Youth will be asked to complete a single CBM session on their home computer at the time of each follow-up assessment, to measure negative bias rather than to reactivate the intervention. Details on the study design and participant flow are displayed in Fig. 1. Some measures (ADIS, PARS, CSSRS, CGAS, CGI-S/CGI-I, and demographics) will be administered by research evaluation staff over the phone, while the remaining self-report measures will be completed online by the parent and/or youth through a study web portal. In some cases when participants are unable or unwilling to complete the phone interview or online assessment, they may be mailed a survey packet to complete at home instead.

**Fig. 1 Fig1:**
[figure not shown]
Participant Flow Diagram

To promote adherence and follow-up completion participants receive Amazon gift certificates for completing baseline and each planned follow-up. Assessment staff made multiple calls to ppts to schedule or follow-up on any missed assessments.

Research evaluation staff will be blinded to CBM allocation and whether they receive AP calls. We have procedures to reduce the chance that research evaluation staff are made aware of subjects’ status (i.e., data sent from the participant’s performance on the CBM program will be sent directly to the programmers’ server and kept separate from the rest of the study data).

### Measures

#### Youth anxiety

The **Anxiety Disorders Interview Schedule for Children (ADIS-C)** [34, 35] is a semi-structured interview developed to identify the presence, severity, and level of interference of anxiety disorders in children aged 6–18 years old. It will be administered to youth and parents to yield Diagnostic and Statistical Manual of Mental Disorders (DSM) diagnoses of generalized anxiety disorder (GAD), social phobia (SP), and/or separation anxiety diagnoses needed to qualify for participation in the study. The trial primary outcome was also derived from this ADIS assessment: anxiety diagnosis remission at the 6-month follow-up. The ADIS will only be administered at the baseline, 6-month, and 12-month interviews. Before conducting ADIS interviews, staff must reach a criterion of 100% diagnostic correspondence with a senior staff on two consecutive interviews. All interviews will be digitally recorded; a random 10% of baseline assessments completed by each evaluation staff will be re-rated by a senior staff member.

The **Pediatric Anxiety Rating Scale (PARS)** [36] is a secondary outcome measure. This 50-item measure integrates youth and parent report of the severity of anxiety symptoms, as well as related functional impairment. Several versions of PARS scoring are available and used in the literature. To allow for comparison with other similar studies, we will calculate a total PARS score as the sum of items 2–7, with a total score ranging from 0 to 30 [37]. The PARS has high inter-rater reliability, fair internal consistency and test-retest reliability, convergent and divergent validity, and sensitivity to treatment effects [36, 38].

The **Screen for Child Anxiety Related Emotional Disorders (SCARED)** [39] is a 41-item measure of anxiety symptoms with youth- and parent-reported versions, with scores of > 25 indicating significant anxiety (total range 0 to 82). The SCARED has been validated in diverse clinical and community samples, with good internal consistency, and has detected clinical improvement in randomized clinical trials of treatment for youth anxiety [38]. We will examine the SCARED as a secondary outcome in this trial.

The **child avoidance measure – self (CAMS) and parent (CAMP)** [40] is an 8-item measure of a child’s tendency to avoid behavior that may cause fear, worry, or anxiety. Children are prompted with “When I feel scared or worried about something …” (or parents “When my child is faced with something that makes him/her feel scared or worried …” ) and asked to indicate their responses on each item using a 4-point Likert-type scale (0 = almost never; 1 = sometimes; 2 = often; 3 = almost always). Items are intended to cover passive avoidance, delay, and active refusal.

#### Depression

Youth and parents will both report on youth depression symptomatology on the **Patient Health Questionnaire (PHQ-9)** [41, 42] which yields depression symptom totals and a provisional DSM diagnosis. Parents will also complete the PHQ-9 to report on their own symptoms of depression. The PHQ-9 will be investigated as a secondary outcome and as a potential moderator of CBM effects.

#### Other psychopathology, improvement

We will assess overall clinical status with the 7-point **Clinical Global Impression (CGI)** Severity and CGI-Improvement scales [42]. The CGI provides a brief assessment of the patient’s overall psychiatric illness before and after initiating a medication or treatment. The CGI-S measures the severity of illness and will be assessed at baseline. At follow-up, the CGI-I will be used as a complementary measure to assess improvement in psychiatric illness after initiating treatment. A CGI-I score of < 2 (very much or much improved) is considered a response to treatment.

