##### Statistical analysis

For each continuous outcome (anxiety symptoms [PARS, SCARED], depression [PHQ-9], psychopathology severity [CGI-S], psychosocial functioning [CGAS]) we will test whether there are differences between arms in the trajectories across time by fitting growth curve models in a nested two-level hierarchical linear model (HLM [64–66];).We will test the primary outcome (anxiety remission based on ADIS-C) and the CGI-I with a generalized form of HLM, using a logit link and the binomial distribution. For all HLM models, the first level of the model represents within-person variation and will include time as a predictor (3–5 timepoints, depending on the measure). The second model level represents between-person variation and includes dummy indicators for arm as the predictor variables. A significant coefficient for arm on the slope of time indicates (i.e., the cross-level interaction of arm by time) that there are different trajectories across time for each arm and will be followed with a graph to interpret the interaction(s). Assuming that the trajectories are nonlinear as is common in clinical trials (e.g., initial intervention effect upon completing the intervention and maintenance period), we will use fractional polynomials to estimate the most appropriate function for time [67, 68]. We will test our primary hypotheses using linear contrasts of the dummy vectors representing treatment arm to determine whether both High-Ratio CBM arms (2 and 3) have a different trajectory than the Low-Ratio arm, and whether High-Ratio CBM + AP (Arm 3) has a different trajectory than High-Ratio CBM Only (Arm 2). Differences at 1 month in acceptability (PAQ) and client satisfaction (CSQ-8) will be tested with a one-way ANOVA with treatment arm as the independent variable and the same a priori contrasts described above.

We will conduct the moderator analyses by adding the moderator and moderatorXarm product in the level-two HLM equation discussed above. A significant coefficient for the interaction term on the slope of time would indicate a moderator effect and will be followed up with graphs of the simple effects to determine the nature of the effect modification.

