We conducted power analyses for the primary outcome (via PASS software [77]) to generate the sample required to detect the hypothesized contrasts in a logistic regression model. For our main comparison of the two High-Ratio CBM conditions versus Low-Ratio CBM, with α = .05, we would have 80% power to detect a 20% greater remission (odds ratio = 2.90) in arms 2 + 3 compared to the Low-Ratio arm with 187 participants (n~ 63 per arm) at the 6-month follow-up**.** For the comparison of the two High-Ratio CBM conditions, at an alpha level of .05, we would have 80% power to detect a 16% greater remission (odds ratio = 1.94) in the CBM + AP arm compared to the CBM only arm with 148 participants per arm (*N* = 444 total) at the 6-month follow-up. We based our target sample on the larger N needed to adequately test this latter hypothesis (Arm 2 vs. Arm 3). To compensate for the loss in precision from imputing data for those lost to follow-up, we inflated the target sample size based on an attrition rate of ~ 10% (*N* = 498, or *n* = 166 per arm). This is a conservative adjustment, as the SEs from imputed data results will be less than the SEs from a complete case analysis.

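### The CGI-I response cut-off is printed as below 2, which on a 1-to-7 scale leaves out the much-improved category that the same sentence counts as response

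*Protocol article*

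**What the plan says.** Under *Other psychopathology, improvement*, the protocol article introduces both scales of the Clinical Global Impression (CGI) and gives their length: "We will assess overall clinical status with the 7-point". The severity scale (CGI-S) is taken at baseline. For follow-up, "the CGI-I will be used as a complementary measure to assess improvement in psychiatric illness after initiating treatment". The response rule comes next: "A CGI-I score of < 2 (very much or much improved) is considered a response to treatment". The article gives this rule nowhere else and never prints the numeric codes of the seven categories.

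The assessment schedule (Table 1) places the CGI-I at 1, 3, 6 and 12 months and the CGI-S at baseline only.

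Under *Statistical analysis*, the article says: "We will test the primary outcome (anxiety remission based on ADIS-C) and the CGI-I with a generalized form of HLM, using a logit link". The same sentence names a binomial distribution, so the CGI-I is analysed as a binary variable, and the response rule is the only dichotomy offered for it.

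**The concern.** The sentence gives one definition twice, once as a number and once in words, and on the usual coding the two select different youths. An analyst who follows the number and one who follows the words will build different endpoints from the same ratings.

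At stake is the response rate on the CGI-I. Under the literal number, the rate in each arm drops by the share of youths rated much improved, and the contrast between arms becomes a contrast in the single best category. A discrepancy left open until the data are in hand also leaves a choice between two response definitions that should have been closed beforehand.

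**Working it through.** **Step 1. Which scores satisfy the rule?** The inputs are the 7-point length, the threshold and the two categories named in the gloss, all from *Other psychopathology, improvement*. The codes are an assumption, so both plausible codings are shown.

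| Coding | Scores below 2 | Scores of 2 or less | Which matches the words? |
|---|---|---|---|
| 1 to 7 (1 = very much improved) | 1: very much improved | 1, 2: very much improved, much improved | 2 or less |
| 0 to 6 (0 = very much improved) | 0, 1: very much improved, much improved | 0, 1, 2: also minimally improved | below 2 |

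The printed threshold agrees with its gloss only under zero-based coding. Nothing in the article indicates that coding for the CGI-I, although the article does print zero-based ranges for other instruments (the child avoidance measure and the Insomnia Severity Index).

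**Step 2. Is the sign meant as strict?** In *Design*, randomization is "stratified by age at recruitment (< age 15 vs. > = age 15". There an inclusive inequality is spelled out next to a strict one. This favours reading the CGI-I sign as strict, but only weakly, because a sign typed as two characters survives conversion more easily than a single symbol does.

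**Step 3. Does any stated design figure depend on the rule?** No. Under *Power analyses*: "We conducted power analyses for the primary outcome (via PASS software [77"], and the primary outcome is ADIS remission. The 148 per arm, the total of 444 and the inflated 498 stand whichever CGI-I cut-off is used. There is no CGI-I power figure to reproduce.

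**Step 4. Illustration of scale for the CGI-I alone.** The assumptions are:
- True response is 34% versus 50%. This pair is chosen to mirror the 16-point difference and odds ratio of 1.94 that the article uses for ADIS remission in Arm 3 versus Arm 2. Check: (0.50/0.50) / (0.34/0.66) = 1.94.
- n = 148 per arm, two-sided alpha 0.05, simple comparison of two proportions.
- A share s of responders scores 2, the same in both arms. The literal rule keeps a fraction 1 − s of each rate.

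Power = Φ[(d − 1.96 × SE0) / SE1], where d = p2 − p1, SE0 = √(2p̄(1 − p̄)/n), p̄ is the mean of p1 and p2, and SE1 = √(p1(1 − p1)/n + p2(1 − p2)/n).

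| s | p1 | p2 | d | SE0 | SE1 | Power |
|---|---|---|---|---|---|---|
| 0 (words applied) | 0.340 | 0.500 | 0.160 | 0.0574 | 0.0566 | about 80% |
| 40% | 0.204 | 0.300 | 0.096 | 0.0505 | 0.0502 | about 48% |
| 60% | 0.136 | 0.200 | 0.064 | 0.0435 | 0.0433 | about 31% |

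Neither the response rates nor the values of s come from the article, and the planned analysis is a repeated-measures logit model. The table shows direction and rough scale only.

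**The case against.** The strongest reply is that the sentence corrects itself. The words name the two response categories, so a careful analyst would count much improved as response. The error does harm only if someone codes the symbol and ignores the words beside it, and no derivation code is available to show that anyone has. This stands as a limit on the likely consequence. It does not make the printed threshold right.

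A second reply is that a less-than-or-equal sign was lost in typesetting or text conversion. That is possible: no single-character inclusive sign appears anywhere in the text at hand, and the gloss itself suggests that one was meant. The document cannot settle the question. As it reads, number and words still disagree, and no other section corrects them.

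A third reply is that zero-based coding would remove the conflict. That is arithmetically true, but the article gives no sign of it, and an unusual coding would itself need stating.

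A reader might infer more than the document supports, in two ways:
- **That the CGI-I is the only global clinical rating after baseline.** It is not. Table 1 and *Psychosocial functioning, quality of life* show the evaluator-rated CGAS at every follow-up. The CGI-I is only the sole CGI rating at follow-up.
- **That the trial's power or main conclusion is damaged.** It is not. The secondary outcomes listed under *Design* name the CGI-S and not the CGI-I, and the sample size rests on ADIS remission. The power losses above rest on rates borrowed from that ADIS calculation.

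**Conclusion.** The contradiction is real and lies within one sentence, given a 1-to-7 coding with 1 as the best category. On that assumption the numeric rule selects one category and the verbal rule two. The difference matters to an analysed endpoint, because the CGI-I is modelled as binary.

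The severity is minor to moderate. The effect is confined to CGI-I response rates and comparisons. Their size cannot be fixed from the document, because it depends on how many youths are rated much improved. Whether a strict sign was intended, or would ever reach the analysis, cannot be determined from the article.

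**What to change.** State the rule as a CGI-I score of 2 or less (very much or much improved), print the seven category codes with their labels, and confirm that the derivation code for the binary CGI-I variable uses the same rule. If the study does use zero-based codes, keep the printed threshold and state the codes.

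The cost is one symbol, one line of category codes and one check of the derivation code. No change to the sample size, the primary analysis or data collection is needed. The correction should be recorded before CGI-I results are examined by arm.
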